#### Coping self-efficacy

Coping self-efficacy will be measured using the CSES, which is a 13-item measure of an individual’s confidence to cope with life challenges [50]. The women are asked to indicate how confident they are to show different coping behaviors in situations where they are confronted with problems. The items are scored on an 11-point Likert scale (0 = ‘cannot do at all’, 5 = ‘moderately certain can do’ and 10 = ‘certain can do’).

#### Impact of genetic test result

To assess the subjective impact of the test result we will use the IES (revised version) [51, 52]. The scale covers three dimensions of symptoms often reported after trauma: intrusion, avoidance, and persistent hyperarousal. The women will be asked to rate the experience of 22 symptoms of traumatic stress over the past week. Response options are ‘not at all’, ‘rarely’, ‘sometimes’, and ‘often’.

#### Self-concept

The BRCA-SC will be used to assess the changes experienced by *BRCA1/2* carriers in their perceptions of themselves [53]. The BRCA-SC is a 17-item scale with response options ranging from 1 = ‘strongly disagree’ to 7 = ‘strongly agree’. It consists of three subscales for stigma, vulnerability, and mastery. The questionnaire was translated into German by the research team following the TRAPD methodology [54].

### Participant timeline {13}

Women who are potentially eligible for the study but have not yet been tested for a *BRCA1/2* gene mutation will be informed about the study at their appointment for collecting the blood sample for genetic testing. Approximately 4 weeks after collection of the blood sample, the women have an appointment to discuss the test results with their physicians. During this appointment, only women with a positive *BRCA1/2* test result will be invited to participate in the study, and their informed consent will be obtained. Women who have previously been tested positive for *BRCA1/2* at a different facility from the six study centers will be invited to participate during their first consultation at the respective study center. Women who are *BRCA1/2* mutation carriers and have already joined the intensified breast-cancer screening program will be invited to participate during their semi-annual appointment. Physicians will complete a recruitment form in which they can also document reasons for non-participation.

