For *BRCA1/2* mutation carriers, the decision between prophylactic surgeries and/or joining the screening program is based upon age of the woman, memories of family cancers, fertility and desire to have children, caring for children, close relationships, body image, ongoing risk and survival, among others [13–17]. For example, in one study, over a third of women who had undergone prophylactic mastectomy reported a decrease in their level of body satisfaction [17]. The same women showed significant decreases in their emotional concern about developing breast cancer. In case of the screening program, about 10% of MRI examinations result in unclear findings and require further imaging and examination [6]. This often results in high levels of anxiety in women [18] even though the majority (75%) of the results turn out non-cancerous [6, 19].

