### Eligibility criteria {10}

Women aged 25–60 years with diagnosed, clearly pathogenic *BRCA1/2* mutations and sufficient knowledge of the German language, who have not been diagnosed with breast or ovarian cancer, and who sign the consent form will meet the inclusion criteria.

Women with an unclear sequence variant in the *BRCA1/2* genes (variant of unclear significance (VUS) I-ARC class 3), women who have already been diagnosed with breast or ovarian cancer, women age under 25 years and over 60 years, with cognitive impairments and/or insufficient knowledge of the German language will be excluded from the study.

Nurses are eligible to lead the decision coaching if they have a specialized qualification as a breast care nurse or have other significant work experience in the field of gynecologic oncology. Additionally, they will complete training specifically developed to qualify nurses to lead decision coaching.

Physicians who will recruit women into the study are eligible to do so after having completed communication training (see the “Optimized standard care” section).

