##### Evidence-based decision aid

The evidence-based decision aid (DA) used in this study has been developed in a prior project funded by the NRW Centre for health Landeszentrum Gesundheit Nordrhein-Westfalen (LZG.NRW). Results of an RCT testing the effectiveness of the decision aid alone are currently pending. The aim of the DA is to enhance knowledge of the benefits and risks of the individual options (intensified breast screening, prophylactic surgery, and no action). The DA is based on evidence-based information and integrates the current findings of risk communication by using fact boxes and presenting risks as natural frequencies. It was developed by experts in the field and pilot tested by affected women before entering the RCT.

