### Outcomes {12}

The primary outcome of the study is the congruence between the preferred and actual role in the decision-making process as measured by the Control Preferences Scale (CPS) [40, 41]. Secondary outcomes are satisfaction with the actual role, decisional conflict (Decisional Conflict Scale (DCS)) [42, 43], knowledge and attitude towards preventions strategies (Multidimensional Measure of Informed Choice (MMIC)) [44, 45], stage of decision-making (Stage of Decision Making Scale (SDMS)) [46, 47], symptoms of anxiety and depression (Hospital Anxiety and Depression Scale (HADS)) [48, 49], coping self-efficacy (Coping Self-Efficacy Scale (CSES)) [50], subjective impact of the test result (Impact of Event Scale (IES)) [51, 52], and self-concept of *BRCA1/2* carriers (BRCA Self-Concept scale (BRCA-SC)) [53]. The instruments that will be used to measure these outcomes will be obtained at three different time points. Baseline measures will be obtained before randomization within a week of inclusion in the study, t1 measures will be obtained 12 weeks after inclusion, and t2 at 6 months after inclusion in the study. Table 1 displays the outcome parameters and time points for outcome measurements.

**Table 1 Tab1:** Outcome parameters

	Study period						
	Enrolment		Allocation	Post-allocation			
Timepoint		Directly after inclusion		1 week after inclusion	Within 3 weeks after inclusion	12 weeks after inclusion	6 months after inclusion
Enrolment							
Eligibility screen	X						
Informed consent	X						
Allocation			X				
Interventions							
Decision aid				X			
Decision coaching					X		
Assessments		t0				t1	t2
Control Preferences Scale							
Desired role		X					
Actual role						X	
Satisfaction						X	
Decisional Conflict Scale		X				X	X
Multidimensional Measure of Informed Choice							
Attitudes		X				X	X
Knowledge		X				X	X
Stage of Decision Making Scale		X				X	X
Hospital Anxiety and Depression Scale		X				X	X
Coping Self-Efficacy Scale		X				X	X
Impact of Event Scale		X				X	X
BRCA Self-Concept Scale		X				X	X

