#### Congruency between desired and actual role in the decision process and satisfaction with the actual role

The congruence between the desired and actual role in the decision-making process and satisfaction with the actual role played is assessed by the Control Preferences Scale (CPS) [40, 41]. The CPS was designed to measure the degree of control that patients want to assume in physician–patient interactions and has often been used in studies on decision support. The items were adapted to the decision situation of *BRCA1/2* mutation carriers by replacing the term “treatment” with “prevention strategy”. The desired role will be measured at baseline and the actual role at T2 (12 weeks after inclusion). The difference between these two measurements reflects the congruence between desired and actual role. One item will be added to the CPS to measure satisfaction with the actual role played at T2.

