#### First and second follow-up

Women in both groups will receive the first and second follow-up questionnaire after 12 weeks and 6 months of genetic diagnosis, respectively. Women in the CG will be informed about the group allocation during the scheduling of the second physician encounter, so that they no longer wait for an appointment for the decision coaching. The questionnaires will be sent by mail with a prepaid envelope attached to return the questionnaire. For a schematic overview of the participant timeline see Fig. 1.

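### One section times follow-up from genetic diagnosis instead of inclusion, and the primary t-test ignores how far women had already decided at baseline

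*Protocol article*

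**What the plan says.** **Who is enrolled.** Participant timeline {13} gives three routes. Newly tested women are invited when they receive a positive result. Women tested earlier "at a different facility from the six study centers will be invited to participate during their first consultation at the respective study center". Carriers who "have already joined the intensified breast-cancer screening program will be invited to participate during their semi-annual appointment" form the third route. Eligibility criteria {10} sets age, mutation and language conditions and admits women "who have not been diagnosed with breast or ovarian cancer, and who sign the consent form will meet the inclusion criteria"; it asks neither for an open decision nor for a maximum time since the test result.

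**What is being decided.** The decision aid covers "intensified breast screening, prophylactic surgery, and no action". Screening is therefore one of the options under decision. The Background notes that "the decision between prophylactic surgeries and/or joining the screening program is based upon age of the woman", so the options can be combined.

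**When the outcome is measured.** Outcomes {12} states that "t1 measures will be obtained 12 weeks after inclusion, and t2 at 6 months after inclusion in the study", and Table 1 agrees. The section on the Control Preferences Scale says: "The desired role will be measured at baseline and the actual role at T2 (12 weeks after inclusion". The First and second follow-up section says that women in both groups "will receive the first and second follow-up questionnaire after 12 weeks and 6 months of genetic diagnosis, respectively".

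**How it is analysed.** Statistical methods {20a} compares mean congruence between arms at t1 by a one-sided independent-samples t-test on group allocation. The Stage of Decision Making Scale is collected at t0, t1 and t2 (Table 1), and its last category is a choice already made. No use of it in the primary analysis is stated.

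**The concern.** There are two linked issues.

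The first is an internal contradiction about when the primary outcome is collected. For a woman recruited when she gets her result, diagnosis and inclusion fall together and the choice of anchor hardly matters. For a woman tested elsewhere, or one already attending semi-annual screening, diagnosis comes earlier by an unstated and variable interval. A centre or mailing office that worked from the follow-up section would send the 12-week form too early relative to inclusion and to the coaching, and in some cases would find the due date already past. The conflicting visit labels add to the risk, because T2 means 12 weeks in one section and t2 means 6 months in another.

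The second concerns the mix of women. Some women on the screening route may, at 12 weeks, describe a role that they played wholly or partly before randomisation. To that extent the intervention has less room to act, and their answers add variation that has nothing to do with allocation. A baseline measure of this is collected before randomisation, but the primary test does not use it.

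**Working it through.** **Step 1: the time anchors side by side.**

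| Place in the protocol article | Anchor | Label for 12 weeks |
|---|---|---|
| Outcomes {12}, text and Table 1 | inclusion | t1 |
| Control Preferences Scale section | inclusion | T2 |
| Decisional conflict section | not stated; assessments numbered T1, T2, T3 | T2, if T1 is baseline |
| First and second follow-up | genetic diagnosis | first follow-up |
| Statistical methods {20a} | not restated | t1 |

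Inclusion is the anchor in every place but one. Write g for the weeks from diagnosis to inclusion. Under the diagnosis anchor, the first follow-up falls 12 − g weeks after inclusion. For a newly tested woman g is about 0 and the anchors agree. For g above 12 the due date precedes enrolment. The article gives no bound on g for the other two routes.

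**Step 2: reproduce the planned size.** Sample size {14} gives d = 0.3, alpha 0.05, power 0.8 and 30% dropout, for a total of 398. Power of the two-sample t-test comes from the noncentral t distribution:

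- One-sided: 139 per arm, 278 in total; 278 / 0.7 = 397.1, rounded up to 398. This matches.
- Two-sided, as the sample size section words it: 176 per arm, 352 in total; 352 / 0.7 = 502.9, rounded up to 503. This does not match.

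So 398 corresponds to the one-sided test in Statistical methods, with 139 analysed per arm. The one-sided/two-sided mismatch is a separate matter. It is noted here because it fixes the starting power.

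**Step 3: illustrate the dilution.** Assumptions not in the article: a share f has no possible effect, d = 0.3 applies to the rest, the SD is unchanged, and f is equal in both arms. Then the overall effect is d(f) = 0.3 × (1 − f). The noncentrality is d(f) × √(139/2), with 276 degrees of freedom.

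| f | d(f) | Power, one-sided (planned) | Power, two-sided |
|---|---|---|---|
| 0 | 0.30 | 80% | 70% |
| 10% | 0.27 | 73% | 61% |
| 30% | 0.21 | 54% | 41% |
| 50% | 0.15 | 35% | 24% |

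The gap between 80% and 70% in the first row comes from the sidedness mismatch alone and should not be charged to recruitment from screening.

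**Step 4: is stage at t0 a valid covariate?** Baseline data and allocation has women return the baseline questionnaire before they are randomised. Stage at t0 is therefore a pre-randomisation variable and can be adjusted for without bias.

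**The case against.** **On the decision.** A reader might infer that for women in screening the role was fixed before randomisation and cannot respond to coaching. The documents do not support that. The Background treats surgery and screening as combinable. The programme is for breast cancer, so joining it does not settle salpingo-oophorectomy. Women in both arms have at least one further physician consultation after inclusion in which the decision can be communicated (Explanation for choice of comparators; Second physician encounter). Coaching starts by asking where the woman stands, so mixed stages are expected. This objection stands: the problem affects some of these women, to an unknown degree.

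**On bias.** A reader might also infer that the comparison is confounded. It is not. Randomisation balances these women on average, and broad enrolment is an openly stated and defensible choice. What remains is possible dilution and avoidable variation.

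**On the figures.** The share, the zero effect within it and the constant SD are all assumed. The sample size section does not restrict d = 0.3 to undecided women. Read as the average effect in the whole mixed population, it already contains any dilution, and the planned 80% stands. This limits the table to an illustration.

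**On the analysis.** Covariates are often left to an analysis plan. That is fair in general, but the article does name its primary test, and that test uses allocation. The same section brings in demographic data, but neither decision stage nor recruitment route.

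**On timing.** The diagnosis anchor appears once, and the label T2 carries its own definition of 12 weeks. The likely intention is clear. The sentence is nonetheless the one that describes sending the questionnaires, and it is wrong for two of the three routes.

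**Conclusion.** The timing contradiction is established from the text alone. One section anchors the questionnaires to diagnosis and the others to inclusion. The difference matters for women tested elsewhere or already in screening. It does not show that any form was actually sent at the wrong time. The visit labels conflict as well.

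The analysis point holds in a limited form. Some women recruited from screening may have made part or all of their decision before randomisation. This may dilute the effect, and the primary test leaves unused a baseline variable that captures it. The size cannot be determined because the article does not give the share. Under the stated assumptions, planned one-sided power falls from 80% to 73%, 54% or 35% at shares of 10%, 30% or 50%; two-sided, from 70% to 61%, 41% or 24%. The documents do not support a claim that the trial is underpowered by any particular amount.

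**What to change.** 1. In First and second follow-up, count 12 weeks and 6 months from inclusion.
2. Use t0/t1/t2 throughout, changing both the Control Preferences Scale section and the Decisional conflict section. Correcting only one would leave the other inconsistent.
3. Replace the primary t-test by a linear model of congruence on allocation, adjusted for stage of decision-making at t0 and, where recorded, recruitment route (new result, tested elsewhere, already in screening). Fix this before the data are analysed.
4. Report the effect by baseline stage, with the arm-by-stage interaction, as a supporting analysis only. No power is shown for it.

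Adjustment removes variation explained by stage; it does not restore an average effect that is truly diluted. The analysis by stage would show whether that has happened.

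Two further changes may suggest themselves and are better avoided. Rewording the role items would alter the primary instrument after recruitment has begun. Adding a role item at t2 only for women undecided at t1 would select on a status that the intervention may itself change.

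**Cost.** Items 1 and 2 are text corrections. Items 3 and 4 need no new patient data for stage, which is already on the t0 form. Route can be used if the centres' recruitment forms record it.

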#### Baseline data and allocation

After recruitment, women will be given the first questionnaire to take home. After sending back their baseline questionnaire, they will be randomized into one of the two groups. Randomization will be performed on a patient basis after the consultation or breast cancer screening, in order to ensure equal treatments by the physician in both groups.

#### Intervention group

Women in the IG will be notified shortly after returning their baseline questionnaire. They will be invited to schedule an appointment with the qualified nurse for the decision coaching. Additionally, they will be sent the patient decision aid. The decision coaching will be scheduled to take place within 3 weeks of giving informed consent.

#### Second physician encounter

Both groups will receive a second physician encounter. In the IG, women will communicate their preferred choice to the physician. In the CG, women will have an additional opportunity to ask questions. This was designed to ensure equality of treatment in both groups. The second physician encounter may take place over the phone.

#### First and second follow-up

Women in both groups will receive the first and second follow-up questionnaire after 12 weeks and 6 months of genetic diagnosis, respectively. Women in the CG will be informed about the group allocation during the scheduling of the second physician encounter, so that they no longer wait for an appointment for the decision coaching. The questionnaires will be sent by mail with a prepaid envelope attached to return the questionnaire. For a schematic overview of the participant timeline see Fig. 1.

**Fig. 1 Fig1:**
[figure not shown]
Participant timeline

### Sample size {14}

The sample size calculation for the summative evaluation is based on an assumed small to moderate effect of the intervention (Cohen’s *d* = 0.3) in a two-sided *t*-test between two groups [28]. It accounts for a drop-out rate of 30%, a power of 0.8 and an alpha error of 0.05. Based on these numbers, the software G*Power [55, 56] yielded a total *n* = 398 (199 participants per group).

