**Methods/design:**

A randomized controlled trial will be conducted in order to compare usual care with structured decision support alongside usual care. The decision support program entails nurse-led decision coaching as well as an evidence-based patient decision aid. Nurses are qualified by a 4-day training program in informed decision-making and decision coaching. Six centers for Familial Breast and Ovarian Cancer in Germany will be included in the study, with a planned sample size of 398 women.

The primary outcome is the congruence between the preferred and the actual played role in the decision-making process as measured by the Control Preferences Scale. It is hypothesized that the structured decision support will enable women to play the preferred role in the decision-making process. Secondary outcomes include the knowledge and attitudes about preventive options, decisional conflict, depression and anxiety, coping self-efficacy, impact of event, and self-concept. A process evaluation will accompany the study.

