### Trial design {8}

The trial is designed as a multicenter superiority parallel group trial with a 1:1 allocation ratio. Randomization will take place on an individual basis.

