## Statistical methods

### Statistical methods {20a}

Baseline data will be analyzed to guarantee comparability of both groups. Mean differences of the primary outcome in both groups (congruence between preferred role at baseline and actual role in the decision-making process at t1) will be compared using an independent samples one-sided *t*-test with the group allocation as the independent variable. All secondary outcomes will be analyzed via independent samples *t*-tests, Chi-square tests, or nonparametric tests in case of non-normality. Beyond group allocation, demographic data will be used as the independent variable. All data analysis will be performed with SPSS and R.

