### Protocol non-adherence and missing data {20c}

Data analysis will be conducted according to the intention-to-treat method. Imputation of missing data is not planned. Additionally, a per-protocol analysis is planned as a sensitivity analysis to exclude participants who did not comply with the allocated intervention by missing the decision coaching or by failing to return all questionnaires.

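### The 398 women do not follow from the stated two-sided calculation: the figure fits a one-sided 5% test, and two-sided power with 30% drop-out is about 70%, not 80%

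*Protocol article*

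**What the plan says.** Under *Sample size {14}*, the protocol article says the calculation is "based on an assumed small to moderate effect of the intervention" (Cohen's d = 0.3) "in a two-sided *t*-test between two groups". It adds: "It accounts for a drop-out rate of 30%, a power of 0.8 and an alpha error of 0.05". The software result is reported as 398 in total, "199 participants per group". The abstract repeats the total ("with a planned sample size of 398 women").

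Under *Statistical methods {20a}*, the group means of the primary outcome "will be compared using an independent samples one-sided *t*-test with the group allocation as the independent variable". No significance level is given there, so the 0.05 in the sample size section is the only alpha in the document.

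*Trial design {8}* describes a "multicenter superiority parallel group trial with a 1:1 allocation ratio". On missing data, *Protocol non-adherence and missing data {20c}* says: "Imputation of missing data is not planned".

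**The concern.** Two things do not fit together. The sample size section names a two-sided test and the analysis section a one-sided test for the same primary outcome. The printed sample size also agrees with the second description and not with the first, which is the one it is said to rest on.

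The sidedness decides whether the trial succeeds in a borderline case. A result in favour of the intervention with a one-sided p-value between 0.025 and 0.05 would count as superiority under one section and not under the other. If this stays open, the choice can be made after the data are seen. Readers of the sample size section are also told that the trial has 80% power for a test on which it has clearly less.

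**Working it through.** **Inputs, all from the protocol article.** d = 0.3, alpha 0.05, power 0.80, drop-out 30%, total 398 (199 per group), all from *Sample size {14}*; 1:1 allocation from *Trial design {8}*. Women who drop out are taken as not analysed, because no imputation is planned (*{20c}*).

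**Step 1: evaluable women per group.** The normal approximation is n = 2(z_alpha + z_power)²/d². The noncentral t distribution gives the exact value for a t-test.

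- Two-sided 5%: 2(1.960 + 0.842)²/0.09 = 174.4, so 175. Noncentral t: 175.4, so **176 per group, 352 in total**.
- One-sided 5%: 2(1.645 + 0.842)²/0.09 = 137.4, so 138. Noncentral t: 138.1, so **139 per group, 278 in total**.

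**Step 2: allow for 30% drop-out and compare with 398.**

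| Test | n/(1 − 0.30), rounded up per group | n × 1.30, rounded up per group | No inflation |
|---|---|---|---|
| Two-sided 5% | 176/0.7 = 251.4, so 252; total 504 | 228.8, so 229; total 458 | 352 |
| One-sided 5% | 139/0.7 = 198.6, so **199; total 398** | 180.7, so 181; total 362 | 278 |

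Inflating the two-sided total instead of each group gives 352/0.7 = 502.9, so 503, which cannot be split equally. No two-sided version comes near 398. The one-sided version matches both the per-group figure and the total.

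**Step 3: power of the trial as sized.** With 30% loss, 199 × 0.7 = 139.3, so 139 evaluable per group. The noncentrality is d × √(n/2) = 0.3 × √69.5 = 2.50.

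- Two-sided 5%: **0.703** (normal approximation 0.706).
- One-sided 5%: **0.802** (normal approximation 0.804).
- One-sided 2.5%: **0.703**.

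**Step 4: what would restore 80% two-sided power.**

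- A larger effect: with 139 per group, d = 0.337.
- Less drop-out: 1 − 352/398 = 11.6% at most, against the planned 30%.
- More women: 504 − 398 = 106 in addition.

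With no drop-out at all (199 analysed per group), two-sided power would be 0.847.

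**Step 5: false-positive risk for a superiority claim.** A two-sided 5% test puts 2.5% in the direction that favours the intervention. A one-sided test at 5% puts the whole 5% there, which is twice as much.

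**The case against.** The best defence is that the trial was meant to be one-sided throughout. The only section that specifies the primary analysis says so, the main hypothesis in *Objectives {7}* is directional, and 398 fits a one-sided 5% test exactly. On that reading one word in the sample size section is wrong and the planned test has its 80% power. Two further points can be made. The 70% depends on the full 30% being lost. And since the analysis section gives no alpha, a one-sided test at 2.5% is not excluded, in which case the false-positive risk is not doubled.

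Much of this stands as a set of conditions. The 70% applies if the test is two-sided (or one-sided at 2.5%) and drop-out is as planned. The 5% false-positive risk applies if 0.05 is spent one-sided. That 398 came from a one-sided calculation is an inference from an exact match, which only the sponsor can confirm.

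It does not remove the problem, because no reading makes all the statements true together. Two-sided at 5%, the 80% power is wrong. One-sided at 5%, the description of the test in the sample size section is wrong, and the lower bar for superiority is given no justification. One-sided at 2.5%, the alpha, the sidedness and the power in that section are all wrong for the test to be run. Nor can drop-out be waved away: 30% is the protocol's own planning figure, and its *Discussion* expects that control women may be more inclined to leave. A separate analysis plan could settle the test, but it could not make 398 follow from the inputs printed here.

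**Conclusion.** The plan is wrong as written. The stated inputs require 504 randomised women, not 398, and the primary test is defined in two contradictory ways.

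If the primary test is two-sided at 5%, the planned trial has about 70% power at d = 0.3, and 80% power only from about d = 0.34. If it is one-sided at 5%, it has about 80% power, but the chance of falsely declaring superiority is 5% where the sample size section implies 2.5%.

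These figures assume a t-test on group means with equal groups, 30% loss in each group, and no contribution from women who are lost. The sidedness of the primary test decides how the main result is read, so this must be fixed before the data are analysed.

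**What to change.** In *Statistical methods {20a}*, make the primary test two-sided at 5%, in line with the sample size section, and report the group difference with a 95% confidence interval.

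In *Sample size {14}*, replace the power statement. For example: 398 women randomised with 30% drop-out leave about 139 evaluable per group, which gives about 70% power at d = 0.3, or 80% power at d = 0.34, in a two-sided 5% t-test. The sponsor should check its own calculation and say, if confirmed, that 398 was obtained with a one-sided setting.

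If the sponsor prefers to keep a one-sided test, the protocol needs its alpha and a justification, and the sample size section must describe that test. At 2.5% one-sided the power is again about 70%. At 5% the doubled false-positive risk should be stated openly.

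The cost is wording in two paragraphs and a less favourable power figure. No extra participants are needed for the correction. Keeping 80% two-sided power at d = 0.3 with 30% drop-out would take 106 more women, which is a separate decision for the sponsor.
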